**Methods:**

We will conduct a prospective multi-centre, cluster-randomized parallel group trial including 1500 patients and 150 recruiting general practitioners. The intervention group will have access to the GAP portal. The portal will contain brief guides for patients and physicians on how to improve the consultation as well as information on epidemiology, aetiology, symptoms, benefits and harms of treatment options for acute, sub-acute and chronic lower back pain. The GAP portal will be designed to be user-friendly and present information on back pain tailored for either patients or physicians in form of brief fact sheets, educative videos, info-graphics, animations and glossaries. Physicians and patients will assess their informedness and the physician-patient communication in consultations at baseline and at two time points after the consultations under investigation. Days of sick leave and health care costs related to back pain will be compared between control and intervention group using routine data of company health insurance funds.

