
#### Procedures for patients

In both IG und CG all patients with back pain receive brief study information at their first consultation and are invited to participate in the study. If interest is expressed, the physicians will inform the patients and enrol them in the study. Each enrolled patient will receive a patient number consisting of a three-digit practice number, a two-digit physician number and a two-digit patient number (e.g. 543/09/01). This number matches the number of their questionnaire. Each physician receives questionnaire packages for 10 patients including: envelope with the t0 and t1 questionnaires and the log-in name for the portal (if patient is in IG). The packages are prepared by the Section of Health Care Research and Rehabilitation Research (SEVERA) on the basis of a pseudonymised list of all participating practices. After enrolling a patient, the medical practice immediately contacts the UHE and forwards the questionnaire number (patient number), contact information, written consent for study participation and permission for data usage to the UHE. Written consent must be received by the UHE in order to allow the UHE to send the t2 questionnaire along with a book voucher 3 weeks after consultation. Patients in IG and CG complete questionnaires on informedness, physician-patient communication, health literacy and self-efficacy at three measurement points: in the doctor’s office before (t0) and after (t1) consultation and 3 weeks later by post (t2). Patients in the CG receive consultation and care as usual not limited or influenced by this study. For patients in the IG the physician uses the explanatory material of the back pain portal, selects information and sends it as a printout or by email. The doctor encourages the patients to study the provided material, to access the online portal and to implement the given recommendations. With the log-in name received in the practice, patients in the IG can access the portal after their consultation. Usage frequency of the portal per patient is checked via web analytics and serves as indicator for intervention adherence. There are no other restrictions or requirements by the study protocol for additional care of the patients in the IG. Further consultations are covered by the health care system. Doctors and patients of the IG are free to continue using the portal during the study. Compensation for using the portal in consultation can only be charged once per patient. 50 randomly selected patients from the IG will be interviewed by SEVERA after completion of the postal survey (t2) in semi-structured 45- to 60-min telephone interviews on acceptance, quality and practicability of the portal as well as satisfaction with the counselling process and the perception of their own and the physician’s communication. Numbers and reasons of discontinuation of intervention and of lost to follow up will be given (Fig. 1).

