*Secondary outcomes* are assessed by questionnaires (survey data) and routine data from the insurance companies (Table 3). Secondary patient outcomes are self-reported self-efficacy regarding their own communication behaviour, health literacy, pain intensity, and days of sick leave and back pain related costs for the health care system. Since t0 and t1 of the patient survey are close together, outcomes of informedness, self-efficacy, and health literacy at t1 are only assessed via global questions. Secondary outcomes for physicians in the IG are the concordance of provided and needed information, the usability of the platform and their actual use of it. Correlation of physician and patient data is possible, as the used items and questionnaires are similar. Differences between CG and IG are additionally analysed regarding the secondary outcomes. Table 3 also contains additionally assessed variables.

**Table 3 Tab3:** Secondary outcomes and control variables

	t_0-physician_	t_0-patient_	t_1-patient_	t_2-patient_	t_3-patient_	t_1-physician_	t_2-physician_
Secondary outcomes (survey data)							
Self-reported self-efficacy (patient)							
Perceived Efficacy in Patient-Physician Interactions (PEPPI)-Questionnaire [48]		X		X			
One Item of Perceived Efficacy in Patient-Physician Interactions (PEPPI)-Questionnaire [48]			X				
Health Literacy (patient)							
Health Literacy Questionnaire (HLQ) [31, 49]		X		X			
Health literacy global questions			X				
Pain intensity (patient)							
Visual analog scale (VAS) [50]		X		X			
Accordance of provided and needed information (physician)							
Domains “Adequacy of information” and “Usability of information” of the Decision Attitude Scale^a,b^ [51]						X	
Self-developed item whether content fits expectations						X	
Usability (physician)							
System Usability Scale (SUS)^a,b^ [52]						X	
Self-developed items on usability						X	
Use of portal (physician)							
Self-developed items on actual use of portal^b^						X	X
Secondary outcomes (routine data)							
Patient’s days of sick leave					X		
Patient’s back pain related costs for the health care system					X		
Control variables (survey data)							
Patient							
Back Belief Questionnaire [53]		X					
Sociodemographic data		X	X	X			
Internet Use		X					
Medical data		X		X			
Physician							
Sociodemographic data	X						
Structural features of the practice (kind of practice, patients per quarter, number of employees, location and region)	X						

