#### Sample size calculation

A priori calculation of the sample size to test the IG’s superiority to the CG in primary outcomes (comparison of adjusted mean values in two groups) was performed with the software *“Power and Precision*”. We used an effect size of 0.30, power of 0.80 and a Bonferroni adjustment (5% / 2 = 2.5%) due to the multiple testing of two primary outcomes. The design effect due to clustering of the practices [30] is DE = 1 + 0.01 × (10–1) = 1.09 with an assumed intra-cluster correlation of 0.01 [31] and a number of cases per cluster of *N* = 10. With a 2:1 distribution in the IG and CG, a sample size of *N* = 320 (IG) and *N* = 160 (CG) without design effect and *N* = 349 (IG) and *N* = 175 (CG) with design effect was calculated. Due to an expected dropout of approximately 35% a sample size of *N* = 537 (IG) and *N* = 270 (CG) is necessary. However, health economics evaluation including a budget impact analysis requires a relatively large variance of cost values (150% standard deviation). Based on a power of 0.80, an alpha level of 5% and an effect size of 30%, the number of cases is *N* = 590 (IG) and *N* = 295 (CG) without design effect and *N* = 643 (IG) and *N* = 322 (CG) with design effect. Given the assumed dropout of approximately 35%, this results in the desired recruitment target of *N* = 1.000 (IG) and *N* = 500 (CG).

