### Generation and concealment of allocation sequence and implementation of allocation

The participating practices are allocated in a 2:1 ratio of IG to CG. The allocation will be stratified by number of participating physicians within a practice (1 physician vs. 2–4 physicians vs. more than 4 physicians). The allocation sequence will be computer generated and concealed until time of allocation. The UHE will recruit the practices, while the MPS will generate the allocation sequence. The UHE will send a list with the research numbers of the practices and the stratification characteristics to the MPS which adds the information about group allocation according to the randomly generated sequence.

The UHE will inform the practices about their allocation. This procedure ensures that neither the recruiting nor the analysing institutes can influence that a particular practice will be allocated to either IG or CG.

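### The practice-level design effect of 1.09 uses the per-physician quota of 10 as its cluster size, so the stated cost power is too favourable once practices average more than about 1.1 to 1.7 physicians

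*Protocol article*

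**What the plan says.** Under Sample size calculation, the protocol article attributes the inflation to practices: "The design effect due to clustering of the practices [30] is DE = 1 + 0.01 × (10–1) = 1.09". The inputs are an ICC of 0.01 "and a number of cases per cluster of *N* = 10". The factor is applied to the analysable numbers: 320/160 becomes 349/175 for the primary outcomes, and 590/295 becomes 643/322 for costs. Dividing by the retained 65% then gives 537/270 for the primary outcomes. For costs it leads to the recruitment target of 1000/500.

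Three other places bear on cluster size:

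- Procedures for patients: "Each physician receives questionnaire packages for 10 patients". The abstract agrees, with a trial "including 1500 patients and 150 recruiting general practitioners", which is 10 per physician.
- Generation and concealment of allocation sequence: practices are randomised 2:1, stratified by participating physicians as "1 physician vs. 2–4 physicians vs. more than 4 physicians".
- Statistical methods, patients' questionnaire data: the model has two levels, patients within practices.

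The text gives neither the number of practices nor the mean number of physicians per practice. Fig. 1 is not included in the text at hand.

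**The concern.** A design effect for practices needs the number of patients per practice. The figure of 10 belongs one level lower, to the physician. The two coincide only if every practice contributes one physician, and the stratification scheme plans for practices that contribute several. At 10 per physician, the three strata mean 10, 20–40 and at least 50 recruited patients per practice.

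The design effect rises with cluster size, and rises further when cluster sizes vary, so the mismatch makes the printed figures too favourable. It matters most for costs. That calculation sets the recruitment target and has little slack: 1000 × 0.65 = 650 analysable in the intervention group against 643 required. A null cost result would then be read against a stated 80% power that the design may not have had.

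**Working it through.** **Inputs from the protocol article.** ICC 0.01; 10 patients per physician; 35% dropout; 2:1 allocation. Primary outcomes: d = 0.30, alpha 2.5%, power 80%. Costs: 30% difference with SD 150%, so d = 0.30/1.50 = 0.20; alpha 5%, power 80%. Two-sided tests reproduce the plan's figures.

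**Step 1: reproduce the plan.** Control-group size = (1 + 1/2) × (z_alpha + z_power)² / d².

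- Primary: 1.5 × (2.241 + 0.842)² / 0.09 gives 159 (159.3 with the t distribution; stated 160). × 1.09: 320 → 348.8 and 160 → 174.4, stated 349/175. Divided by 0.65: 537/270.
- Costs: 1.5 × (1.960 + 0.842)² / 0.04 gives 295, hence 590/295. × 1.09: 643.1/321.6, stated 643/322. Divided by 0.65: 990/496, rounded up to 1000/500.

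All stated figures follow from the stated inputs. The only input in question is the cluster size.

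**Step 2: where 80% cost power ends.** With 650/325 analysed, the largest tolerable design effect (DE) is 650/590 = 1.102. Solving 1 + 0.01 × (m − 1) = 1.102 gives m = 11.2 patients per practice.

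- Counted as recruited (10 per physician): 11.2/10 ≈ 1.1 physicians per practice.
- Counted as analysed (10 × 0.65 = 6.5 per physician): 11.2/6.5 ≈ 1.7 physicians per practice.

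The analysed count matches the plan's own sequence better, because the design effect is applied before the dropout inflation. On that count the factor 1.09 itself is adequate up to 10/6.5 ≈ 1.5 physicians.

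**Step 3: range over assumed physicians per practice, equal sizes, ICC 0.01.** DE = 1 + 0.01 × (m − 1). Recruits needed = (590 + 295) × DE / 0.65, each arm rounded up. Power = Φ(0.20 / √[DE × (1/650 + 1/325)] − 1.960).

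| Physicians per practice (assumed) | Analysed m | DE | Recruits needed | Cost power | Recruited m | DE | Recruits needed | Cost power |
|---|---|---|---|---|---|---|---|---|
| 1 | 6.5 | 1.055 | 1437 | 81.8% | 10 | 1.09 | 1485 | 80.5% |
| 2 | 13 | 1.12 | 1526 | 79.4% | 20 | 1.19 | 1622 | 77.0% |
| 3 | 19.5 | 1.185 | 1614 | 77.2% | 30 | 1.29 | 1757 | 73.6% |
| 5 | 32.5 | 1.315 | 1791 | 72.8% | 50 | 1.49 | 2030 | 67.4% |

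**Step 4: unequal sizes.** Assume, for illustration, 60% of practices with 1 physician, 35% with 3 and 5% with 5. The mean is 0.6 + 1.05 + 0.25 = 1.9, the mean square is 0.6 + 3.15 + 1.25 = 5.0, and the size-weighted mean is 5.0/1.9 = 2.63. Analysed m is 6.5 × 2.63 = 17.1, DE 1.16, power about 78%. Recruited m is 26.3, DE 1.25, power about 75%.

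**Step 5: patient primary outcomes.** At recruited m = 20, 30 and 50 they need 879, 954 and 1101 recruits in total, all below 1500. At 650/325 analysed and DE 1.49, power is 91.6%; every other scenario in the table is higher.

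**The case against.** The strongest reply is that the consequence is small and rests on a number the article does not give. This largely stands. On the analysed count, 10 per practice already covers about 1.5 physicians, and at 2 physicians cost power falls less than one point short. An average of 5 would place the typical practice in the top stratum, which nothing in the text supports; that row only bounds the range. Costs are a secondary outcome. The patient model allows for practice clustering, so the validity of the patient-outcome tests is not in question. Costs also come from insurer records rather than returned questionnaires. If those were complete for all 1500 patients, cost power would be about 92% at 2 physicians and about 85% at 5 (recruited count). The plan nevertheless applies 35% dropout to costs, so this softens the point without answering it.

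A reader might infer three stronger things that the documents do not support:

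- That any average above one physician per practice loses the 80%. Step 2 shows that it does not.
- That the ICC of 0.01 was borrowed from an unsuitable outcome, because the same reference appears beside the Health Literacy Questionnaire in Table 3. A shared citation does not show which outcome the value describes, and the source is not available here.
- That the plan's arithmetic is wrong. Every figure reproduces.

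**Conclusion.** The inconsistency is definite: a practice-level design effect is computed with a physician-level count, in a plan whose strata expect several physicians per practice. Its direction is also definite. Its size is conditional on physicians per practice, which is not stated.

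The stated cost power is too favourable once practices average more than about 1.7 physicians (analysed count) or about 1.1 (recruited count), assuming equal practice sizes and the plan's ICC and dropout. On the better-matched analysed count, the loss from 80% is under 1 point at 2 physicians, about 3 at 3 and about 7 at 5. On the recruited count it is about 3, 6 and 13 points. Unequal sizes add to this. The printed primary requirements (349/175 and 537/270) depend on the same factor, but the 1500 patients cover them throughout. It would therefore be wrong to read this as a threat to the patient primary comparisons.

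**What to change.** State the expected number of practices and the analysed patients per practice, as a mean m and coefficient of variation CV. Recompute DE = 1 + ((1 + CV²) × m − 1) × ICC at practice level. Replace 1.09, 349/175, 537/270, 643/322 and the 80% cost power with the resulting figures for the fixed 1500 patients. The replacement values cannot be computed from the article, because m and CV are absent; the trial team would have to supply them. If ICC values above 0.01 are shown, label them as a sensitivity range.

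No patients need to be added and the design does not change. The cost is one recalculated paragraph and, probably, a slightly less favourable stated power for costs.

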### Generation and concealment of allocation sequence and implementation of allocation

The participating practices are allocated in a 2:1 ratio of IG to CG. The allocation will be stratified by number of participating physicians within a practice (1 physician vs. 2–4 physicians vs. more than 4 physicians). The allocation sequence will be computer generated and concealed until time of allocation. The UHE will recruit the practices, while the MPS will generate the allocation sequence. The UHE will send a list with the research numbers of the practices and the stratification characteristics to the MPS which adds the information about group allocation according to the randomly generated sequence.

The UHE will inform the practices about their allocation. This procedure ensures that neither the recruiting nor the analysing institutes can influence that a particular practice will be allocated to either IG or CG.

### Blinding/masking

Due to the nature of the intervention, participants (physicians, patients) will be aware of their allocation status and cannot be blinded. Also, the assessment of the evaluators cannot be blinded, since the number of cases will differ between IG and CG, questionnaires for the IG will contain additional variables, and it is possible that further questions regarding the routine data of the health insurance arise.

### Data collection methods

In addition to interviews and the health insurance routine data, the intervention is mainly assessed using questionnaires completed by patients and physicians (Additional file 3: Characteristics of survey instruments). The practices will receive a detailed instruction manual in order to ensure standardised collection of data.

### Data management

A seven-digit patient research ID (three-digit number for the practice, two-digit number for the attended physician and a consecutive two-digit number per patient attending the physician) is allocated to each participating patient. A database with these research IDs and the associated names and contact details of the patients (participation list) is created. Due to the research IDs the questionnaires of the three measurement points can be matched. Further, the research IDs of the questionnaires are definite relatable to the log-in names of the portal (user data) and the research IDs used for the routine data of the health insurance. The analysing institutions keep a record about the return of the patient questionnaire in an Excel-Sheet. The ID of returning questionnaires will be reconciled with the ID of cases in the SPSS data files.

Codebooks will be prepared for the questionnaires. Scanning is used for the data entry of the patient questionnaires. The team member entering the data can immediately correct data which was incorrectly inserted by the computer system. The data of 10% randomly selected questionnaires will be double-checked. If more than 5 ‰ of the data entries are incorrect, all data will be entered twice. The patient questionnaires will be checked for plausibility of age and gender. The checks include that the gender is reported identically across all three measurement points and that there is only 1 year of difference between the measurement points t0 and t2. For all items there will be a range check of data values. As the physician questionnaires are completed primarily online, there will be no double entry of data but there will be plausibility checks comparable to the patient questionnaires.

### Statistical methods

#### Analysis of patients‘questionnaire data

Based on the analysis of the missing outcome data, simple or multiple imputation may be considered. Dropout analysis will be performed using Chi-Squared tests for nominal variables, Mann–Whitney U tests for ordinal variables and t-tests for interval variables. The significance level is set at *p* = 0.05. Special attention is paid to the hierarchical data structure of the questionnaire data. Due to the cluster randomisation, patients’ responses cannot be presumed as independent, as the patients are nested within practices. Because of this, separate two-level (patient – practice) multilevel linear models for both measurement points (t1 and t2) will be calculated. Treatment allocation (IG vs. CG) will be used as predictor variable in the multilevel linear models. The fit of the multilevel linear models are tested using amongst others the Akaike’s information criterion and Schwarz’s Bayesian criterion. Despite the randomisation a propensity score adjustment is considered in case of a potential imbalanced allocation [32]. Intraclass correlations are calculated to assess the cluster (practice) dependency of the responses.

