### Participants and recruitment

Together with the *Bavarian Association of Family Physicians and General Practitioners,* the *Institute of General Practice at the University Medical Center Erlangen* (UHE) will recruit a total of 150 general practitioners (GP) from practices in Northern Bavaria. Two-thirds of the practices are randomized to the IG and one third to the CG. If a GP practice expresses interest after being invited to participate in the study, it receives information concerning the study, regulations for enrolling in the intervention program, and participation documents for the GP practice and the patients. After written consent to study participation and enrolment in the intervention program, the practice is formally included in the GAP trial. The UHE passes on registration data to the *Bavarian State Association of company health insurance fund*, which is responsible for the cooperation with the participating company health insurance funds. Over five quarters (July 2018 to September 2019), the GP practices are to recruit a total of 1000 patients for the IG and 500 for the CG. With an average share of at least 20% BKK insured persons, 900 patients per practice license in Bavaria and a back pain prevalence of almost 30%, the resulting recruitment potential is 50 to 60 patients per physician. The fact that physicians receive reimbursement for recruitment and patients receive a book voucher will facilitate sufficient recruitment.

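### The patient model has no physician level: the arm comparison stays valid, but some precision may be lost and the practice intraclass correlation may blend two correlations

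*Protocol article*

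**What the plan says.** All references are to the protocol article.

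- **Model.** Under Analysis of patients' questionnaire data, "separate two-level (patient – practice) multilevel linear models for both measurement points (t1 and t2) will be calculated". On the fixed part, "Treatment allocation (IG vs. CG) will be used as predictor variable in the multilevel linear models".
- **Reported correlation.** The same section adds: "Intraclass correlations are calculated to assess the cluster (practice) dependency of the responses".
- **Randomisation.** "The participating practices are allocated in a 2:1 ratio of IG to CG", and allocation is "stratified by number of participating physicians within a practice", with strata of one, two to four, and more than four. The sponsor therefore expects practices with several physicians.
- **Numbers.** The trial "will recruit a total of 150 general practitioners (GP) from practices in Northern Bavaria". The number of practices and the mix of physicians per practice are not given. Procedures for patients supplies each physician with questionnaire packages for 10 patients.
- **Outcomes.** In Table 2 the patient-rated communication instruments at t1 (SDM-Q-9, KOVA, P.A.INT satisfaction scale) concern the physician consulted. Patient informedness, the other primary domain, is a self-report.
- **Identification.** Under Data management the patient ID contains a "two-digit number for the attended physician and a consecutive two-digit number per patient attending the physician".

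**The concern.** Up to 10 patients judge the same physician's communication, and some practices contribute several physicians. Two patients of one physician are then likely to give more similar ratings than two patients of different physicians in the same practice. A model with only a practice intercept treats both pairs as equally alike.

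Two things follow if the physician component is not zero. First, the model gives practices with several physicians less weight than is optimal, so the treatment estimate may be less precise than the data allow. Second, the one correlation it estimates falls between the same-physician and the different-physician value. A reader could not recover either without knowing this trial's mix of physicians per practice.

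**Working it through.** **1. The plan's own figures.** Sample size calculation uses effect size 0.30, power 0.80, alpha 0.025 (two-sided assumed) and 2:1 allocation.

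- Control group: 1.5 × (2.2414 + 0.8416)² / 0.30² = 158.4, so 159, with 318 in the intervention group (stated 160 and 320).
- Design effect: 1 + 0.01 × 9 = 1.09. Then 320 × 1.09 = 348.8 (stated 349) and 160 × 1.09 = 174.4 (stated 175).
- Dropout of 35%: 349/0.65 = 536.9 and 175/0.65 = 269.2, so 537 and 270.

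The figures reproduce. The design effect is described as clustering by practice, but its cluster size of 10 is the number of packages per physician. A practice with five physicians would hold 50.

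**2. Inputs for the comparison.**

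- From the document: 150 physicians, 10 patients each, 35% dropout (10 × 0.65 = 6.5, so about 7 evaluable), intraclass correlation 0.01.
- Assumed, because not stated: physician components of 0.01, 0.05 and 0.10; practice components of 0 and 0.01; and two mixed sets of practices, each adding to 150 physicians:
  - 89 practices: 60 with 1 physician, 15 with 2, 6 with 3, 3 with 4, 5 with 6.
  - 66 practices: 30 with 1, 15 with 2, 10 with 3, 6 with 5, 5 with 6.

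**3. Formulae.** Let a practice have k physicians with m patients each, practice component b, physician component p, total variance 1, and c practices of size k.

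- True variance of the practice mean: v = b + p/k + (1 − b − p)/(km).
- Variance assumed by the two-level model: u = r + (1 − r)/(km), where r is the single correlation to which maximum likelihood converges under the true structure.
- Three-level variance of the estimate: proportional to 1/Σ(c/v).
- True variance with two-level weights: proportional to Σ(cv/u²) / [Σ(c/u)]².

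With the same mix in both arms, the 2:1 factor cancels from the ratio.

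**4. One case by hand: 89 practices, m = 7, p = 0.05, b = 0, giving r = 0.0225.**

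- v = (0.05 + 0.95/7)/k = 0.1857/k, so the three-level variance is 0.1857/150 = 0.001238.
- u for k = 1, 2, 3, 4, 6 is 0.1621, 0.0923, 0.0690, 0.0574, 0.0458.
- Σ(c/u) = 370.1 + 162.5 + 86.9 + 52.3 + 109.2, about 780.9.
- Σ(cv/u²) is about 781.3.
- Two-level variance = 781.3/780.9² = 0.001281. The ratio 0.001281/0.001238 is 1.035, a loss of 3.5%.
- The model-based variance is 1/780.9 = 0.001281, equal to the true variance, so the test is calibrated.

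**5. Other cases.** These use 998 evaluable patients (998/150 = 6.65 per physician). Loss is 1/relative efficiency − 1.

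| Practices | p | b | Relative efficiency | Variance loss | Two-level correlation | Same physician / different physician |
|---|---|---|---|---|---|---|
| 66 | 0.01 | 0 | 0.9989 | 0.1% | 0.003 | 0.01 / 0 |
| 66 | 0.05 | 0.01 | 0.9816 | 1.9% | 0.027 | 0.06 / 0.01 |
| 89 | 0.05 | 0.01 | 0.9750 | 2.6% | 0.034 | 0.06 / 0.01 |
| 89 | 0.05 | 0 | 0.9674 | 3.4% | 0.022 | 0.05 / 0 |
| 66 | 0.10 | 0.01 | 0.9456 | 5.8% | 0.048 | 0.11 / 0.01 |
| 89 | 0.10 | 0 | 0.9175 | 9.0% | 0.052 | 0.10 / 0 |

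The 89-practice mix with 7 patients per physician gives 0.2% at p = 0.01, b = 0.

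**6. Where the loss vanishes.** If every practice has the same k and m, then u and v are constant, all practices get equal weight under either model, and the ratio is 1. With one physician per practice the two levels coincide.

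**7. Error rate and power.** Across all scenarios the actual type I error of the two-level test was 0.0245-0.0261 at nominal 0.025. For 89 practices, p = 0.05 and b = 0.01, the standard error is 0.0811 against 0.0800, and power is 0.928 against 0.934.

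**The case against.** The strongest reply is that a model clustering at the unit of randomisation is valid and widely accepted, so a third level is a refinement. That stands. A reader might infer that leaving out the physician level makes the primary test anti-conservative. The documents do not support this: practices are randomised, practice is the modelled cluster, and the calculated error rate stays at its nominal level.

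A reader might also infer that precision is lost in any case. That fails too. The practice mix is not stated, the loss is nil with single-physician or equal-sized practices, and at the planning value of 0.01 it is negligible. Correlations of 0.05 and 0.10 are five and ten times that value. The recruitment target also has slack for the primary outcomes: 537 + 270 = 807 are needed and 1500 are planned, because the cost analysis sets the target.

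Nor is the planned correlation simply wrong. Its stated purpose is to describe dependency within practices, and an average within-practice correlation does that. Finally, the argument is strongest for the communication instruments, since informedness is not a rating of a physician.

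What remains is that the level is expected from the design, identifiable from the ID, and left out of a model the article specifies by its levels. Planned comparison by information criteria does not commit the analysis to examining it.

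**Conclusion.** The point holds as a minor matter of efficiency and reporting, not as a flaw in the primary inference. If practices enter differing numbers of physicians and ratings cluster by physician, the planned model costs about 0.1-0.2% of variance at a physician-level correlation of 0.01, 2-3.5% at 0.05 and 6-9% at 0.10. In the same circumstances its single correlation cannot be read as either component: with 0.06 for the same physician and 0.01 for different physicians, it comes out at 0.027-0.037 in the multi-physician mixes examined.

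These sizes rest on about 7 evaluable patients per physician, the assumed mixes, large-sample approximations and the same mix in both arms. If nearly all 10 patients supply t1 data, the largest standard-error increases found were 3.1% at 0.05 and 6.7% at 0.10, or 1.031² − 1 = 6.3% and 1.067² − 1 = 13.8% of variance. If all practices are single-physician or equal in size, there is no loss.

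**What to change.** Under Analysis of patients' questionnaire data, add a random intercept for physician nested within practice, at least for the communication outcomes. Keep practice as the unit of inference for the arm comparison, and report the physician and the practice variance components. State in advance that the planned two-level model is used if the physician component is estimated at zero or cannot be separated from practice.

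The cost is one further variance parameter and no new data, since the ID already identifies the physician. The downside is a possible boundary or non-converging estimate if few practices enter more than one physician, which the fallback rule covers.
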